### Sample size

The study was designed to detect an increase from 85% to 95% in the proportion of culture-confirmed pulmonary TB cases initiated on appropriate treatment within 30 days. Sample size was calculated with the equation of Hayes and Bennett, using the coefficient of variation (κ) [26]. With κ = 0.05 and a cluster size of 12 culture-positive cases, we would need 16 clusters and 188 culture-positive TB cases in each arm to detect this difference with 95% confidence and 80% power. We assumed 10% of individual participants would be lost to follow-up at 60 days, so we would need 208 culture-positive TB cases in each arm. Based on the assumption that 25% of TB suspects would have a positive MGIT culture, we would require enrolment of 1,664 TB suspects. The total sample size will therefore be 32 clusters and 1,664 individual participants.

The coefficient of variation (κ) is small, but as the clusters are clinic time blocks rather than geographic areas or health care facilities, minimal variation is expected between clusters. This value of κ corresponds to a range of proportions appropriately treated within 30 days in the district hospital laboratory arm of 77-94%.

For the secondary endpoint of all-cause mortality within 60 days, the analysis will incorporate all participants (all suspects), regardless of presence or absence of TB disease. The sample size of 32 clusters and 60 participants per cluster gives approximately 80% power to detect a 33% reduction in mortality from 12% in the district hospital laboratory arm to 8% in the point-of-care arm, with 95% confidence.

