The development of novel molecular tools, in particular the Xpert® MTB/RIF assay, offers new opportunities to tackle these problems. This is a fully automated, closed cartridge diagnostic system that utilises hemi-nested polymerase chain reaction (PCR) and molecular beacon technology to detect the presence of *Mycobacterium tuberculosis* and rifampicin-resistant mutations directly from clinical samples in less than 2 h [16-18]. The World Health Organization (WHO) recommended the system be implemented in high-burden settings on the basis of initial data from validation and demonstration studies [19-21]. Many countries are now moving ahead with implementation and there is a need for research to address key questions in the early phase of implementation so as to inform future scale-up [21]. One critical question relates to the optimal positioning of the diagnostic system within different health systems, and this is the focus of the research study.

The primary objective is to test the hypothesis that timely initiation of appropriate TB treatment when the diagnostic system is positioned at the primary health care clinic (point of care) is different from when the diagnostic system is positioned centrally at the district hospital laboratory. Secondary objectives are:

•To evaluate the impact of Xpert MTB/RIF positioning on additional clinical outcomes (mortality, hospital admission, time to initiation of antiretroviral therapy)

•To explore the cost-effectiveness of Xpert MTB/RIF implementation at primary health care clinic level

•To compare the operational feasibility of Xpert MTB/RIF placement at the primary health care clinic level and district hospital laboratory level.

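### The stated 80% power for 60-day mortality assumes 60 participants per cluster (1,920), but planned enrolment is 1,664 (52 per cluster), which gives about 75%

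*Protocol article*

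**What the plan says.** All of the relevant statements are in the Sample size section of the protocol article.

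- **Enrolment.** The section works from the primary outcome to an overall target: "The total sample size will therefore be 32 clusters and 1,664 individual participants".
- **Loss.** On the way to that target it allows for attrition: "We assumed 10% of individual participants would be lost to follow-up at 60 days".
- **Mortality population.** For all-cause mortality within 60 days, "the analysis will incorporate all participants (all suspects), regardless of presence or absence of TB disease".
- **Mortality power.** "The sample size of 32 clusters and 60 participants per cluster gives approximately 80% power to detect a 33% reduction in mortality", the reduction being "from 12% in the district hospital laboratory arm to 8% in the point-of-care arm".
- **Method.** The Hayes and Bennett equation with a coefficient of variation κ is named for the sample size. A value of κ = 0.05 is given for the primary outcome. No value is given for mortality.

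**The concern.** Mortality is to be analysed in all enrolled suspects, so its sample is the enrolment target itself. That target is 52 per cluster, yet the power statement uses 60. The two figures are a few sentences apart in one section, and the article neither explains the 60 nor plans to enrol 1,920.

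The power statement also makes no visible deduction for loss, although the 10% loss assumed in the same section is set at 60 days, the mortality time point.

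What is at stake is how far the trial can be relied on to detect the mortality reduction it names. If the stated power is too high, the chance of missing that reduction is larger than a reader is told. Mortality is the only secondary outcome with a power statement.

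**Working it through.** **Inputs**

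- Mortality p0 = 0.12 and p1 = 0.08 (Sample size).
- 32 clusters, taken as 16 per arm (Sample size).
- Cluster size m = 60 as stated for mortality; m = 1,664 / 32 = 52 from the enrolment target; m = 52 × 0.9 = 46.8 if 10% are lost.
- Two-sided 5% test. This is an assumption, from the stated 95% confidence and the non-directional objective in the Background, that treatment initiation under one strategy "is different from when the diagnostic system is positioned centrally at the district hospital laboratory".
- κ = 0.05, borrowed from the primary outcome. This is an assumption for mortality; the range 0 to 0.10 is shown.

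**Formula** (Hayes and Bennett, unmatched clusters, proportions), with c clusters per arm:

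c = 1 + (z_α/2 + z_β)² × V / (p0 − p1)², where V = p0(1 − p0)/m + p1(1 − p1)/m + κ²(p0² + p1²)

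Solved for power: Φ( (p0 − p1) / √(V/(c − 1)) − 1.96 ).

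**Step 1. Check the formula on the primary outcome.** With 85% versus 95%, m = 12 and κ = 0.05, V = 0.1275/12 + 0.0475/12 + 0.0025 × (0.7225 + 0.9025) = 0.018646. Then c = 1 + 2.8016² × 0.018646 / 0.01 = 15.63, so 16 clusters, and 15.63 × 12 = 188 cases per arm. Both match the article. The article's 208 per arm then gives 416 / 0.25 = 1,664, also as stated.

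**Step 2. Reproduce the mortality power at m = 60.** V = 0.1056/60 + 0.0736/60 + 0.0025 × (0.0144 + 0.0064) = 0.0030387. √(V/15) = 0.014233, and 0.04 / 0.014233 = 2.810. Power = Φ(2.810 − 1.960) = 80.2%. The stated figure is reproduced. At κ = 0.05, 60 is the smallest whole cluster size that reaches 80%.

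**Step 3. Use the enrolment target, m = 52.** V = 0.1792/52 + 0.000052 = 0.0034982. √(V/15) = 0.015271, and 0.04 / 0.015271 = 2.619. Power = Φ(0.659) = 74.5%.

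**Step 4. Apply 10% loss, m = 46.8.** V = 0.1792/46.8 + 0.000052 = 0.0038811. √(V/15) = 0.016085, and 0.04 / 0.016085 = 2.487. Power = Φ(0.527) = 70.1%.

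**Step 5. Sensitivity to what is not stated.**

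| Variant | m = 60 | m = 52 | m = 46.8 |
|---|---|---|---|
| κ = 0 | 80.9% | 75.1% | 70.7% |
| κ = 0.05 | 80.2% | 74.5% | 70.1% |
| κ = 0.10 | 78.3% | 72.7% | 68.4% |
| κ = 0.05, t distribution, 30 df | 80.2% | 74.5% | 70.0% |
| κ = 0.05, without the added cluster | 82.7% | 77.2% | 72.9% |
| Clustering ignored | 83.2% | 77.7% | 73.3% |

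No variant reaches 80% at 52 per cluster. Each falls by about 5 to 6 points between 60 and 52.

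**Step 6. Detectable effect.** At κ = 0.05 and 80% power, the fall from 12% has to be to about 7.7% with 52 per cluster, or about 7.5% with 46.8.

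**The case against.** **Only a secondary endpoint is affected, and the text says approximately.** This largely stands as to importance. The primary calculation reproduces, and no enrolment target, allocation or analysis changes. A reader might infer that the trial as a whole is underpowered; the documents do not support that. But 74.5% is not a rounding of 80%: the chance of missing the stated effect goes from about 20% to about 25%.

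**60 might be the enrolled number before loss.** It cannot be. 60 × 0.9 = 54, not 52, and the 1,664 already contains the inflation from 188 to 208 cases per arm. At 54 per cluster power is 76.1% in any case.

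**The 70% figure is pessimistic.** A reader might take 70% as the actual power. The documents do not go that far. The 10% loss is assumed for individual participants at 60 days, so applying it to deaths is reasonable. However, the Outcome evaluation section provides for telephone follow-up, home visits, named contacts, TB registers and the HIV programme database. A contact can report a death when the participant cannot be reached. So 70% is conditional on the full 10% loss; with no loss the figure is about 75%.

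**κ for mortality is unknown.** True. A reader might infer that the 80% arises only if κ = 0.05 was carried over from the primary outcome. It does not: at 60 per cluster, κ = 0 gives 80.9%, and κ = 0.10 without the added cluster gives 80.8%. It is also tempting to show much lower power under strong clustering. No figure in the article supports a large κ for mortality, and the section argues that variation between time blocks at one clinic should be minimal. The finding rests on cluster size, not on κ.

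**Conclusion.** The point holds as an internal inconsistency. The power quoted for 60-day mortality belongs to a sample 256 participants larger than the one planned. For 1,664 participants it is about 75%, and about 73% to 75% for κ from 0 to 0.10, given a two-sided 5% test and the named equation. It is about 70% only if the assumed 10% loss applies in full to mortality.

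The article does not settle whether 60 or 52 reflects the intended recruitment. 1,664 is the figure given as the total and derived step by step, but the authors have to confirm it. This should be fixed; it is not critical, because it changes one secondary endpoint's stated power and leaves the primary sample size as it is.

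**What to change.** Reconcile the 60 per cluster with the 1,664 total. If 1,664 stands, do one of the following:

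- restate mortality power for 12% versus 8% as about 75%, or about 70% if 10% are lost by 60 days, giving the κ used; or
- keep 80% power and restate the detectable effect as a fall from 12% to about 7.7%, or to about 7.5% after 10% loss.

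Either is a change of wording that makes the statement less favourable and needs no extra participants. If 60 per cluster was the intention, the total has to read 1,920, which means 256 more participants, and the question of loss remains to be addressed.

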### Randomisation

The allocation schedule for random assignment of 2-week time blocks was computer generated, using random permuted blocks of eight. Allocation for each clinic block was placed into sealed envelopes by the statistician; the principal investigator opens the envelope on the Friday before the start of a new 2-week block and communicates the allocation for the next 2 weeks to study staff.

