### Statistical analysis

Analysis of baseline characteristics will be performed to characterise the study population and to identify baseline imbalances between the study arms in order to decide whether any covariates need to be adjusted for in the final analyses. The baseline data will include: age, sex, body mass index (BMI), history of previous TB, HIV infection status, CD4+ cell count, and use of antiretroviral therapy and isoniazid preventive therapy.

All final analyses will be intention-to-treat analyses performed at the individual level taking account of within-cluster correlation. The definition of TB cases for the primary outcome will be based on MGIT culture positivity. The proportion of TB cases initiated on appropriate TB treatment within 30 days will be based on whether the appropriate treatment regimen was commenced within 30 days of the initial clinic visit—appropriate regimens are defined according to drug susceptibility pattern and with reference to national guidelines (Table 1) [27]. The primary analysis will include only TB cases not on TB treatment at the time of enrolment, i.e. excluding smear non-converters or failures still on treatment. The primary outcome is a binary variable (initiation of appropriate treatment or not) so univariate logistic regression will be performed as the primary analysis using generalised estimating equations (GEE) with a binomial distribution function and a logit link [28]. The odds ratio will be reported with 95% confidence intervals and a *p*-value from the Wald test. This method will allow for the correlation between observations (within clusters) without needing to specify a distributional assumption for the correlations. In addition, important individual-level characteristics that are unbalanced between arms will be included in the model as covariates. For the secondary outcomes with binary variables, GEE models will also be fitted with a binomial distribution function and a logit link. For the secondary outcomes with time-to-event measures, Cox proportional hazard models will be fitted with the shared frailty option to account for the cluster randomisation [29]. Hazard ratios will be presented with 95% confidence intervals.

**Table 1 T1:** Definitions of appropriate initial anti-TB drug regimen for primary outcome measurement

**Case definition***	**Appropriate initial anti-TB drug regimen**

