Blinding of patients or of health care workers is not feasible in this pragmatic diagnostic trial because allocation to trial arms involves different actions by the patient and the clinical staff. As a result of this, the outcomes are as objective as possible to limit potential bias from differential ascertainment of outcomes in the two arms. The possibility of differential recruitment into the trial arms exists but will be minimised by standardised referral criteria for the clinic health care workers; recruitment will be monitored by reviewing the clinic records to ascertain what proportion of patients with cough were referred to the study during each 2-week block. This will be reported if there is a major imbalance in recruitment to the two trial arms. There is a further risk of selection bias if there is differential non-participation. The proportions of eligible subjects consenting by trial arm will be monitored and will be reported accurately at the conclusion of the trial. There is some risk of contamination between the arms if, over time with point-of-care testing, the health workers see the importance and the effect of receiving the test result in a timely fashion and this then improves their ability to encourage all suspects to return and receive their result. This would tend to bias the findings towards the null hypothesis. We will explore this by assessment of the variability in the proportion returning for their test result by cluster and by time period.

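### The primary GEE leaves out the permuted blocks by which fortnights were randomised, so under a marked time trend its intervals are too wide and some power is lost

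*Protocol article*

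**What the plan says.** The clusters are 2-week periods at one clinic. On their allocation, the Randomisation section says: "The allocation schedule for random assignment of 2-week time blocks was computer generated, using random permuted blocks of eight". Envelopes are opened on the Friday before each new period, so the clusters run in sequence, and a permuted block covers 8 × 2 = 16 weeks.

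On the analysis, the Statistical analysis section says: "univariate logistic regression will be performed as the primary analysis using generalised estimating equations (GEE) with a binomial distribution function and a logit link". The result is an odds ratio with a Wald p-value. Clustering is handled within each fortnight: "This method will allow for the correlation between observations (within clusters) without needing to specify a distributional assumption for the correlations". The only route by which other terms can enter is this: "important individual-level characteristics that are unbalanced between arms will be included in the model as covariates". A permuted block is not an individual-level characteristic, and the design keeps it balanced between arms, so it cannot enter that way.

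The Sample size section expects little variation between fortnights. It translates κ = 0.05 into a range of 77–94% in the hospital laboratory arm. The Discussion plans to look at return for results by cluster and time period, as an exploration of contamination only.

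**The concern.** With one clinic and time periods as clusters, variation between clusters is largely variation over calendar time. Permuted blocks force the arms to be balanced within each 16-week stretch, so a change from one stretch to the next adds almost nothing to the true sampling variance of the treatment effect. A univariate model does not know this. Its sandwich variance measures the spread of all fortnights around their arm mean and counts the between-block change as noise. The design has paid for balance over time, and the stated analysis does not use it.

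At stake are precision and power in a trial sized for 80% power. This is not a detail left to an unseen analysis plan, because the article names the primary model as univariate.

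**Working it through.** **1. The plan's own figure.** Inputs from the Sample size section: 85% v 95%, κ = 0.05, m = 12 cases per cluster, 80% power; two-sided 5% is assumed.

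c = 1 + (1.96 + 0.84)² × [p0(1−p0)/m + p1(1−p1)/m + κ²(p0² + p1²)] / (p0 − p1)²

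The bracket is 0.010625 + 0.003958 + 0.004063 = 0.018646. With (1.96 + 0.84)² = 7.849, c = 1 + 7.849 × 0.018646 / 0.01 = 15.63, so 16 clusters per arm; 15.63 × 12 = 187.6, so 188 cases. The stated size reproduces. Thirty-two clusters make four permuted blocks (4:4 within each is assumed).

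**2. How much of a trend the design removes.** For a straight-line trend over 32 fortnights, the variance of the time index is (32² − 1)/12 = 85.25. Within a block of eight it is (8² − 1)/12 = 5.25. So 80/85.25 = 94% of the trend variance lies between blocks and is balanced by design; 6% remains within blocks.

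**3. Rough size of the error.** Assume drift from 77% to 94%, mean 85.5%, no treatment effect.
- Drift variance: 0.17²/12 = 0.0024 (SD 4.9 points).
- Binomial variance per cluster: (0.855 × 0.145 − 0.0024)/12 = 0.0101.
- Variance the univariate model estimates: 0.0101 + 0.0024 = 0.0125.
- Variance under the blocked design: 0.0101 + 0.06 × 0.0024 = 0.0103.
- SE ratio: √(0.0125/0.0103) = 1.10. The test then rejects at 1.96 × 1.10 = 2.16 true SEs, a type I error of about 3%.

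**4. Simulation of the same drift.** Clusters of about 12 cases, four blocks of eight, small-sample-corrected tests, and the odds ratio for 85% v 95%: (0.95/0.05)/(0.85/0.15) = 3.35. Ranges are over repeated simulations.

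| | Univariate | With block terms |
|---|---|---|
| Type I error, drift 77% to 94% | 3.0–3.2% | 4.9–5.4% |
| SE overstated by | 8–9% | – |
| Power, same drift | 76.9–78.8% | 80.6–82.5% |
| Power, no drift | 88.6% | 87.9% |

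Within each simulation the power gap is 3.6 to 4.6 points.

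**5. Other drifts, with κ = 0.05 cluster noise added** (about 4,000 runs per scenario; each pair is univariate / with block terms). This noise is why power without drift is lower than in step 4.

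| Assumed drift | Univariate mean SE / true SD | Type I error, planned Wald | Type I error, corrected | Power, corrected |
|---|---|---|---|---|
| None | 0.94 | 6.6 / 7.9% | 4.9 / 4.9% | 76 / 75% |
| Linear, 79% to 89% | 0.97 | 6.4 / 8.4% | 4.6 / 5.4% | 75 / 75% |
| Linear, 72% to 93% | 1.07 | 3.7 / 8.1% | 2.7 / 4.7% | 74 / 78% |
| Abrupt step, about 20 points | 1.29 | 1.7 / 8.7% | 1.1 / 5.2% | 71 / 82% |

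The mean log odds ratio under the null was 0.00 to two decimals, or within 0.01 of it, in every scenario, so the univariate estimate is not biased.

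**6. Sparsity of a treatment-by-block test.** At 95% in the point-of-care arm, each block has about 188/4 = 47 such cases. The chance that a block has no failures is 0.95⁴⁷ = 0.090; that at least one of four has none, 1 − (1 − 0.090)⁴ = 31%. In simulation with the 77–94% drift and odds ratio 3.35, an empty failure cell occurred in 56% of trials.

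**The case against.** The strongest reply is that the plan predicts no drift. It expects minimal variation between fortnights, and 77–94% is the total spread implied by κ, not a trend. Its SD is 0.05 × 85% = 4.25 points, while a trend across the whole range has SD 4.9 (CV 4.9/85 = 0.058). The assumed drift therefore uses slightly more than all the planned cluster variation. This stands: the scenario is near the upper end of what the plan's own figures allow, and the documents cannot show that it will occur.

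A reader might infer from the Discussion that drift is expected, since it describes how "over time with point-of-care testing, the health workers see the importance and the effect of receiving the test result in a timely fashion". That sentence is conditional and concerns contamination, a dilution specific to the laboratory arm, which block main effects would not remove. The national roll-out gives no support either, because the Ethical considerations section says the test was not yet installed in the sub-district outside the trial.

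It can also be said that the univariate model with the planned Wald test is closer to 5% than the block-adjusted model with that test: 3.8–4.4% against 8.1–8.5% under the 77–94% drift. This stands as well, and it governs the fix. The near-nominal figure arises because the uncorrected sandwich variance is too small with 32 clusters, which happens to offset the conservatism. That is not a reason to rely on it, but block terms must not be added without the correction.

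**Conclusion.** The mismatch between randomisation and primary model is real and is fixed by the article's own wording. Its effect is limited. A reader might infer that any drift makes the intervals wrong, that the estimate is biased, or that false positives rise. The calculations support none of these. The estimate is unbiased, the error from omitting the blocks is conservative, and with about 10 points of drift it is negligible.

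Under a marked trend (77% to 94%, assumed), the SE is about 8–9% too large, the corrected type I error is about 3%, and about 4 points of power are lost. An abrupt step of about 20 points would cost about 11 points. These figures rest on 4:4 allocation within blocks, consecutive fortnights, about 12 cases per cluster and the assumed shape of the drift. Block terms leave within-block drift in place. The change is worth making because a trial planned at 80% power has little margin and the allocation dates are already held.

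**What to change.** In the primary GEE, add permuted-block indicators as fixed effects, one for each block beyond the first. Use a small-sample-corrected sandwich variance (for example Kauermann–Carroll) and a t reference with degrees of freedom equal to clusters minus parameters: 32 − 5 = 27 for four blocks. State the rule for however many blocks are used. Thirty-two fortnights from 22 August 2011 end about 12 November 2012, whereas enrolment to March 2013 spans about 40 to 42, so there may be more than four. Keep the univariate model, with the same correction (t on 30 degrees of freedom), as a sensitivity analysis.

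Extend block terms to secondary models only where events are not too sparse. Time to MDR-TB treatment is doubtful: at 10% of 2 × 208 = 416 cases there would be about 42. Keep the contamination check descriptive, by cluster and time period. A treatment-by-block test should not serve for it, because empty cells are likely.

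The cost is a few model terms, under one point of power if there is no drift (88.6% v 87.9%), and non-convergence in about 1–2% of simulated trials under drift, for which a fallback should be named. The odds ratio also becomes conditional on block and moves slightly: mean log odds ratio 1.193 against 1.165 under the 72–93% drift.

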### Study design

The study is a pragmatic cluster randomised clinical trial comparing two positioning strategies for the Xpert MTB/RIF system: positioning at centralised laboratory level (district hospital laboratory) versus positioning at primary health care clinic level (point of care). The cluster (unit of randomisation) is a 2-week time block at the primary health care clinic (clinic blocks), and clusters are randomly assigned to the district hospital laboratory strategy or point-of-care strategy. The trial schema is shown in Figure 2.

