### Participants

Adult (≥18 years) pulmonary TB suspects with confirmed HIV infection and/or at high risk of MDR-TB are included after giving informed consent. These criteria were defined because of the high risk for mortality in these groups and prioritisation for Xpert MTB/RIF testing, in line with the WHO recommendations [20]. A TB suspect is defined for the purposes of the trial as an individual with a current cough (of any duration) with or without other symptoms. High risk of MDR-TB is defined according to national and international guidelines and incorporates the following categories: failure of the standard treatment regimen (2HRZE/4HR), failure of the re-treatment regimen (2HRZES/1HRZE/5HRE), acid-fast bacilli (AFB) smear non-conversion at month 2 or 3 of the standard or re-treatment regimen, relapse or return after default, any other previous TB (4 or more weeks of TB treatment), household contact with a known MDR-TB case, prison inmate within the last 12 months and health care worker [24,25]. Participants are excluded if they report a previous diagnosis of MDR-TB or extensively drug-resistant TB (XDR-TB), are severely unwell requiring admission to hospital, or are unable to give informed consent. Participants are recruited between the times of 0800 and 1630, Monday to Friday.

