### Implementation

Health care workers at the primary health care clinic identify potential participants. All individuals reporting cough are referred to the study nurse. Eligibility criteria are checked by the nurse, and subjects meeting the inclusion criteria are provided spoken and written information about the study in isiZulu and/or English; those willing to participate are taken through the informed consent process and are asked to provide a signature or thumbprint on the consent form.

A baseline assessment is performed by the study nurse. Demographic information, current symptoms, previous TB history, risk factors for drug resistance, HIV status, and history of ART use are documented on a case report form.

With both strategies, clinical decisions are made by the study nurse on the basis of the Xpert MTB/RIF result and according to pre-defined algorithms. TB patients without resistance to rifampicin are commenced on standard anti-TB therapy (4HRZE/2HR) by the study nurse. All patients with rifampicin-resistant TB are reported to the trial physician on the same day and are subsequently referred to the specialist drug-resistant TB treatment centre in Durban. Management of suspects with a negative Xpert MTB/RIF follows existing protocols for smear-negative TB suspects: oral antibiotics are prescribed and patients are advised to return if symptoms do not improve after 14 days. Patients who remain symptomatic following this course of antibiotics can be referred to the district hospital for chest X-ray and physician review. Results from MGIT culture and DST are returned through the routine laboratory system and are used to guide clinical management where appropriate.

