## Trial status

The study received final ethical approval in June 2011. Enrolment commenced on 22 August 2011. Enrolment is scheduled to complete in March 2013 and follow-up will be complete in May 2013.

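### The Randomisation text lets staff learn the next arm on the last recruiting Friday of the current block, so a patient could be deferred to Monday into the other arm

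*Protocol article*

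**What the plan says.** - **Unit (Study design).** "The cluster (unit of randomisation) is a 2-week time block at the primary health care clinic (clinic blocks"). Everyone enrolled in a given fortnight is in the same arm.
- **Schedule and release (Randomisation).** The list was "computer generated, using random permuted blocks of eight", and the statistician sealed the allocations in envelopes. Then "the principal investigator opens the envelope on the Friday before the start of a new 2-week block and communicates the allocation for the next 2" (that is, for the coming fortnight); study staff are the ones told. No time of day is stated, and nothing says whether the site knows the permuted block size.
- **Recruiting hours (Participants).** "Participants are recruited between the times of 0800 and 1630, Monday to Friday".
- **Start (Trial status).** "Enrolment commenced on 22 August 2011", which was a Monday.
- **Who enrols (Implementation).** Clinic workers refer everyone with a cough to the study nurse. "Eligibility criteria are checked by the nurse", and those willing to take part then go through consent.
- **Blinding and safeguards (Discussion).** "Blinding of patients or of health care workers is not feasible in this pragmatic diagnostic trial". The authors accept that recruitment or participation may differ by arm. They rely on standard referral criteria and on two checks: "recruitment will be monitored by reviewing the clinic records to ascertain what proportion of patients with cough were referred to the study" in each 2-week block, and the share of eligible people who consent in each arm.

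**The concern.** When allocation goes by calendar time, staff always know the current arm. What can still be concealed is the next one. Once an enroller knows both, the choice between enrolling a patient today and asking for a return on Monday becomes a choice of arm.

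The arms differ in ways that nurse and patient both see. Under the laboratory strategy the patient is asked to return after 72 h; at the point of care the result takes about 2 h. On a Friday before a switch to point of care, a nurse with good intentions might defer someone who seems unlikely to return. The opposite move is possible too. Those moved would probably differ from the rest in ways that affect treatment start, 60-day mortality and hospital attendance. The generalised estimating equations allow for correlation within clusters, not for selection into them, and covariate adjustment reaches only what was measured.

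**Working it through.** **Does the Friday overlap with recruitment?** Enrolment began on a Monday and each block lasts two weeks, so a block runs from Monday to the second Friday. The Friday before a new block is therefore the tenth and last recruiting day of the old one, if the next block follows at once. Recruitment that day is open from 08:00 to 16:30. The Randomisation text allows the envelope to be opened at any hour of that Friday, including those hours.

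**The plan's own figures.** The plan gives none for predictability of the allocation. The totals used below reproduce from its Sample size section:

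- Clusters per arm = 1 + (1.96 + 0.84)² × [0.85×0.15/12 + 0.95×0.05/12 + 0.05²×(0.85² + 0.95²)] / 0.10² = 15.63, so 16.
- Cases per arm = 15.63 × 12 = 187.6, so 188; 188/0.9 = 208.9 (stated as 208).
- Suspects = 2 × 208 / 0.25 = 1,664.

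**Patients exposed per changeover.**

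- 1,664 / 32 = 52 suspects per block.
- 52 / 10 recruiting days = 5.2 suspects on the last Friday.
- 416 / 320 = 1.3 culture-positive cases on that day.
- The mortality calculation in the same section uses 60 participants per cluster, which would give 6.0 per day.

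**How many changeovers are switches?** I assume four arms of each kind in every set of eight (from the planned 16 clusters per arm) and 32 contiguous blocks.

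- Within a set, two neighbouring blocks differ with probability 2 × 4 × 4 / (8 × 7) = 4/7. Seven neighbouring pairs give 4 switches per set, so 16 in four sets.
- Each of the three joins between sets is a switch with probability 1/2, adding 1.5.
- Total: 17.5 of 31, half of them (8.75) from laboratory to point of care.

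Suspects seen on a last Friday before any switch: 17.5 × 5.2 = 91, or 5.5% of 1,664. Before a laboratory-to-point-of-care switch: 8.75 × 5.2 = 45.5, or 2.7%. These are ceilings on who could be moved by this route.

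**What deferral could do: an illustration.** The deferral fractions and the outcomes of deferred patients are my assumptions; the document gives none. Take deferrals at laboratory-to-point-of-care switches only, with a quarter of those deferred culture-positive. Suppose their chance of timely appropriate treatment is 50% under the laboratory strategy and 95% at point of care, and their mortality is 30% and 20%. Base sizes are 208 cases and 832 suspects per arm.

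| Share deferred | Suspects moved | Primary difference (planned 10 points) | Mortality difference (planned 4 points) |
|---|---|---|---|
| 25% | 11.4 | 9.5 | 3.6 |
| 50% | 22.8 | 9.0 | 3.2 |
| 100% | 45.5 | 8.0 | 2.3 |

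For example, at 100% the laboratory proportion becomes (208×0.85 − 11.375×0.50) / (208 − 11.375) = 87.0%, against 95%. Here the effect shrinks. Moving other patients, or moving them the other way, could widen it.

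**Would the planned checks see it?** A patient referred on Friday and asked by the nurse to return on Monday counts as referred. A patient whose referral itself is delayed lowers the old block's referral proportion, but by one or two people in a fortnight's total. A deferral recorded as eligible without consent lowers that arm's consent proportion, pooled over about 16 blocks. Neither check separates the days next to a changeover.

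**The case against.** **No hour is given.** If the envelope is always opened after 16:30, the overlap disappears. That is correct, so the document does not show that the next arm is known during recruitment, only that its rule allows it. An article may leave a clock time to the full protocol. But the article does state the release rule, and in a form that includes recruiting hours.

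**Safeguards exist.** All patients with cough are to be referred, those needing admission are excluded, differential recruitment is openly discussed, and baseline imbalances can be adjusted for. This stands and limits the damage. The monitoring is insensitive to changeover moves; it would be wrong to call it blind to them.

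**The schedule may have gaps.** 32 fortnights are 64 weeks, whereas 22 August 2011 to the start of March 2013 is over 79. Blocks may therefore not all be contiguous, and the count of 17.5 in 31 depends on that.

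**Staff know the current arm anyway.** True, so better timing removes movement between arms, not every route to recruitment bias.

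**A stronger reading to avoid.** A reader might infer from the fixed size of eight that about one fortnight in five is known in advance and open to exploitation. The arithmetic is right: the number of forced fortnights at the end of a set is 1, 2, 3 or 4 with probability 0.571, 0.286, 0.114 and 0.029, a mean of 1.6 of 8 or 6.4 of 32. The inference does not follow. Certainty requires recruiting staff to know the size and where each set begins, and the document does not say that they do. Moreover, only the first forced fortnight in a set is a switch, so 4 of 31 changeovers would be switches known a full block ahead; the other 2.4 or so forced fortnights repeat the current arm and offer no choice.

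**Conclusion.** The point holds as a gap in concealment of the next arm. The written rule permits the person who screens and takes consent to know both arms on the last recruiting day of a block, in an open trial where date decides arm. About 5 suspects per changeover are exposed, at roughly 17.5 of 31 changeovers if blocks are contiguous, allocation is four to four within each set and enrolment runs at the planned rate.

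Any bias is likely to be modest. In the illustration, deferring a quarter to a half of the exposed laboratory patients takes the 10-point primary difference to between 9.5 and 9.0 points, but those figures rest wholly on assumed behaviour and outcomes. The document gives no evidence that anyone was deferred, and a reader should not infer manipulation. The reason to act is that the gap is avoidable at almost no cost in a design that the Discussion defends on grounds of internal validity.

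**What to change.** 1. **Randomisation section.** State that each allocation is opened and communicated only after recruitment closes at 16:30 on the last Friday of the current block, or before opening on Monday. If this is already the practice, say so.
2. **Same section.** State that the permuted block size is not disclosed to recruiting staff.
3. **Check with data already collected.** Compare enrolment numbers and baseline characteristics on the last Friday and the first Monday of blocks, by direction of switch. This also covers blocks already completed.

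The cost is a sentence or two of text and one descriptive table, with no extra patients, visits or staff. The downside is that staff have less notice of the next arm.

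I do not propose a new schedule with varying block sizes. With undisclosed sizes of 4, 6 and 8, fewer than one fortnight in 32 would be certain, but the best guess would still be right about 67.5% of the time, against 66.6% with fixed eights. It would also put at risk the exact 16:16 split that four sets of eight provide.
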